### Data analysis

All data will be de-identified and coded to ensure participant anonymity and it will stored securely on a password protected computer. Participant names, corresponding identification numbers, and contact information will be kept in a separate password protected file on a secure computer at Deakin University. Only the research team will have access to secured information. Only the de-identified data will be used in the analysis phase and in the summary of main outcomes that will be delivered to participants, any subsequent publications, and conference presentations. A data monitoring committee is not needed for this study as it is a non-therapeutic (behavioural) trial using low-risk procedures, and as such, the study team will be monitoring the data.

Analyses will be conducted using an intention-to-treat (ITT) approach [59], with all randomised participants analysed in their allocated group regardless of the intervention uptake. Every effort will be made to minimise missing data and where appropriate, multiple imputation will be used to handle missing data.

Baseline participant’s characteristics will be compared between the intervention and control group using Chi-squared or Fisher’s exact test for categorical variables, and *t* test or Kruskal-Wallis test for numerical variables. Drop-out bias will also be assessed using the same approach but comparing the baseline characteristics of participants with complete data against those lost to follow-up as a function of treatment group.

The intervention effect during the 12-week follow-up on numerical outcomes will be assessed using linear mixed models including group, time (T1, T2 and T3) and group by time interaction as fixed effects and participant as a random effect.

The feasibility of the Step One Program will be determined by the proportion of individuals who completed the baseline survey and were eligible to participate, how often participants read the SMS messages, how often they respond to Sunday SMS messages, and completion of follow-up surveys. Intervention acceptability will be reported by 1) summarising the multiple choice responses to the intervention acceptability questions in the T2 survey, and 2) performing qualitative analysis of the short answer responses and interviews using simple coding to identify recurring patterns and themes.

We will explore whether changes between T1 and T2 in the primary outcomes are correlated with changes in the potential mediator variables.

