## Research objectives

### Hypotheses

Compared to participants who receive generic ‘thank you’ messages, participants in the Step One Program will report at the end of the intervention (4 weeks) and 12 weeks post-intervention:Significantly lower alcohol intake as measured by the Alcohol Use Disorders Identification Test (AUDIT) and self-report of number of standard drinks consumed in the previous 30 days.Significantly higher wellbeing as measured by the Personal Wellbeing Index – Adult (PWI-A).Significantly higher service engagement as indicated by the number of services accessed and frequency of access.

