#### Random allocation

Individuals are screened for eligibility. The first two eligibility criteria are determined in the baseline survey. If an individual responds that they identify as a man or they are aged under 18 years, they will be automatically directed to the end of the survey. The AUDIT score is calculated by [name] once the baseline survey is received. If the individual scores eight or above, they will then receive a welcome email and test SMS message. Once the receipt of both has been confirmed, participants are randomly allocated into the intervention group or the control group using a computer generated block randomisation at a 1:1 ratio with 10 allocations per block to ensure equal numbers in each group if the recruitment goal is not achieved. The sequence of condition allocations are placed in opaque envelopes with participant identification numbers on the front. Once a participant’s eligibility is determined, an envelope is opened by [name] and the participant is allocated to the experimental condition inside the envelope. As participants are blinded, to reduce bias they will not be informed of the number or frequency of messages in the intervention as this information will reveal which group participants have been randomly allocated to.

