### Power analysis

The target sample size is 50 participants per group. Assuming 20% attrition rate, we estimate to collect complete data from 40 participants in each group. Sample size calculations are based on the only available Australian study of alcohol consumption in this population, the Australian Alcohol and lesbian/bisexual women – insights into culture and emotions (ALICE) study [1], which provides estimates for the AUDIT score. A sample size of 40 participants per group has 84% power for detecting a post-intervention mean change of 4 points in the AUDIT score, when the standard deviation is assumed as 6 for two independent groups, two-tailed test, and significance level 0.05. This sample size will achieve 80% power to detect effect sizes larger than 0.63 for any of the other scores outcomes.

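### The planned mixed model leaves the baseline arm difference free and does not adjust for T1, so it gives up precision available at no cost; the stated 84% power is correct arithmetic but is not tied to a named contrast

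*Protocol article*

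**What the plan says.** Numerical outcomes are to be analysed with "linear mixed models including group, time (T1, T2 and T3) and group by time interaction as fixed effects and participant as a random effect" (Protocol article, Data analysis). Time has three levels including T1, group has its own main effect, and participant is the only random effect listed, which most naturally means a random intercept. The section names no contrast and mentions no baseline covariate or constraint.

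The Hypotheses section is worded as a comparison between arms at each follow-up: "participants in the Step One Program will report at the end of the intervention (4 weeks) and 12 weeks post-intervention".

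The Power analysis section states: "A sample size of 40 participants per group has 84% power for detecting a post-intervention mean change of 4 points in the AUDIT score". The inputs behind this figure contain no baseline term; they are set out in these words: "when the standard deviation is assumed as 6 for two independent groups, two-tailed test, and significance level 0.05". The planning values come from an earlier Australian study "which provides estimates for the AUDIT score". The recruitment goal is given as follows: "The target sample size is 50 participants per group". Dropout is then allowed for: "Assuming 20% attrition rate, we estimate to collect complete data from 40 participants in each group". No correlation between visits is given. Allocation is by "computer generated block randomisation at a 1:1 ratio with 10 allocations per block".

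Two other features matter. Entry requires an AUDIT of at least 8 (Eligibility criteria). AUDIT items 3 to 10 refer to the past year at T1, four weeks at T2 and 12 weeks at T3 (Alcohol use and severity).

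**The concern.** When T1 is an outcome level and the arms may differ freely there, the group-by-time coefficient for T2 is a difference between arms in change from baseline. Its variance depends on the T1-T2 correlation. The power calculation contains no correlation: it is a two-sample comparison of one measurement per person. So the sample size section and the analysis section match only under particular readings.

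Randomisation also means that any T1 difference between arms arises by chance. Estimating it freely spends information that could sharpen the treatment effect. In a trial of 100 people, whose authors expect recruitment to be difficult, that precision is worth having. A random intercept alone further implies the same variance at every visit and the same correlation between every pair of visits. The entry cut-off and the changing recall windows make that doubtful for the AUDIT.

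**Working it through.** **Inputs from the article.** 40 per arm with complete data (50 × 0.80 = 40), difference 4 points, SD 6, two-sided 0.05. **Assumed.** The T1-T2 correlation ρ, shown over a range, and, unless stated otherwise, SD 6 at both visits.

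**1. The stated figure.** Two independent means: SE = 6 × √(2/40) = 1.342 and 4/1.342 = 2.98. Power is 83.8% from the noncentral t with 78 degrees of freedom (84.6% by the normal approximation). The stated 84% reproduces.

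**2. Three ways to compare the arms at T2.**
- Arm difference at T2, no baseline: SD = 6, whatever ρ is.
- Difference in change, T2 against T1: SD = 6√(2(1−ρ)).
- Baseline-adjusted difference: SD = 6√(1−ρ²), with 77 degrees of freedom.

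| ρ (assumed) | Change: SD | Change: power | T2 unadjusted: power | Adjusted: SD | Adjusted: power |
|---|---|---|---|---|---|
| 0 | 8.49 | 54.9% | 83.8% | 6.00 | 83.7% |
| 0.3 | 7.10 | 70.1% | 83.8% | 5.72 | 87.0% |
| 0.4 | 6.57 | 76.7% | 83.8% | 5.50 | 89.5% |
| 0.5 | 6.00 | 83.8% | 83.8% | 5.20 | 92.5% |
| 0.7 | 4.65 | 96.7% | 83.8% | 4.28 | 98.5% |

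**3. Where the change contrast reaches the stated power.** It needs 2(1−ρ) ≤ 1, so ρ ≥ 0.5. This threshold is not fixed:
- If the 10 participants per arm with only a T1 survey also enter the model, it is about 0.47.
- If the SDs differ, it is SD₁/(2 × SD₂): 5/12 = 0.42 with SD 5 at T1 and 6 at T2, and 4.5/12 = 0.375 with SD 4.5 at T1.
- With SDs 4.5 and 6 and ρ = 0.40, the change SD is √(20.25 + 36 − 21.6) = 5.89 and power is 85.1%, above the stated figure. The adjusted SD is still 6√(1 − 0.16) = 5.50, with power 89.5%.

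**4. Relative precision with equal SDs.** Adjusted variance over change variance is (1+ρ)/2: 0.65 at ρ = 0.3 and 0.75 at ρ = 0.5. Adjusted variance over unadjusted T2 variance is 1−ρ²: 0.91 at 0.3 and 0.75 at 0.5. Neither ratio exceeds 1. The worst case is ρ = 0, where adjustment costs one degree of freedom (83.7% against 83.8%).

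**5. The same comparison within the three-visit mixed model.** With random-intercept covariance, 40 completers per arm and the normal approximation, constraining the arms to be equal at T1 gives 87.8%, 90.2% and 93.1% at ρ = 0.3, 0.4 and 0.5. The free interaction coefficient gives 71.2%, 77.7% and 84.6%. The T2 arm difference from the free model gives 84.6% at each.

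**The case against.** A reader might infer that the plan tests change from baseline and that its 84% therefore fails unless the correlation is at least 0.5. The documents do not support that. The Data analysis section names no contrast. The arm difference at T2 can be estimated from the same model, it fits the Hypotheses section at least as well, and it keeps about 84% at any correlation. The power statement speaks of a mean change with SD 6; if 6 is the SD of change, 84% again holds at any correlation, although the cited source points to the score. The 0.5 threshold also needs equal SDs at T1 and T2, which the entry cut-off makes doubtful. All of this stands.

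A reader might also infer that the random-intercept model inflates the type I error. For the interaction contrasts that depends on inputs the article does not give. With SDs 4.5/6/6 at T1/T2/T3, correlations (T1-T2, T1-T3, T2-T3) of 0.40/0.35/0.70 gave 6.1% at T2 and 7.6% at T3 by simulation. Correlations of 0.6/0.5/0.6 give 3.6% and 5.8% in a large-sample approximation, and 0.5 throughout gives 4.2% at both. With equal SDs and equal correlations it is 5%. The error can go either way, so no single figure should be claimed.

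It is also fair that the planned model is conventional and unbiased under randomisation, and that keeping T1 as an outcome retains randomised participants who return no follow-up survey, in line with the intention-to-treat statement. The fix should preserve this. Residual covariance and the choice of contrast are often settled in an analysis plan that is not shown, so their absence from an article is not in itself a fault. What remains is what the article does fix: T1 as an outcome level, with a free arm difference and no baseline adjustment.

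**Conclusion.** The concern holds as a matter of precision, not of error. The model as written leaves the T1 arm difference unconstrained and makes no use of T1 to sharpen the follow-up comparison. Under equal SDs of 6 and 40 completers per arm, adjusting would raise power at correlations 0.3, 0.4 and 0.5 by 16.9, 12.8 and 8.7 percentage points over the change contrast (87.0 − 70.1, 89.5 − 76.7, 92.5 − 83.8), and by 3.2, 5.7 and 8.7 points over the unadjusted T2 difference (each less 83.8).

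Power below the stated figure follows only if three conditions hold together: the T2-against-T1 interaction is the test, 6 is the score SD at both visits, and the correlation is below about 0.5. The article settles none of them. This is a free improvement.

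**What to change.** 1. Name the arm differences at T2 and at T3 as the estimates.
2. Keep T1 in the outcome vector but constrain the arm means to be equal at T1; this retains randomised participants without follow-up. Alternatively, model T2 and T3 with the T1 value and its interaction with visit as covariates, together with the multiple imputation already planned, so that those participants are not lost.
3. Use an unstructured covariance across the visits in place of a random intercept alone.
4. State in the Power analysis section that 84% is the power of an unadjusted two-sample comparison at one visit with SD 6, and say whether 6 is the SD of the score or of the change. If a correlation is assumed, give it.

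The cost is wording in the analysis and power sections. No new data, visits or participants are needed, and with three visits and 100 participants an unstructured covariance should be straightforward to fit.

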#### Eligibility criteria

To be eligible, participants need to:Identify as a same-sex attracted woman. This includes transgender women, transgender men, and gender diverse individuals. Transgender men were eligible as these individuals were likely involved in lesbian, bisexual, and queer women’s communities prior to transitioning to male; and if the individual has not undergone gender reassignment surgery, certain female health issues will still affect them.Be aged 18 years or older.Score eight or above on the AUDIT.Own a mobile phone with SMS capabilities and have access to the internet.Respond to both the welcoming email and the test SMS message received after enrolling.

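### The mixed model gives each arm its own T1 mean and names no baseline covariate, so the natural effect contrast is a change-score difference: valid, but less precise than the collected data allow.

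*Protocol article*

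**What the plan says.** Data analysis opens the model sentence with "The intervention effect during the 12-week follow-up on numerical outcomes will be assessed using" and then specifies "linear mixed models including group, time (T1, T2 and T3) and group by time interaction as fixed effects and participant as a random effect". It does not say which term or contrast is the effect, and it names neither a baseline covariate nor a common T1 mean. Baseline is otherwise mentioned through between-arm tests: "characteristics will be compared between the intervention and control group using Chi-squared" and similar tests.

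Power analysis states "A sample size of 40 participants per group has 84% power for detecting a post-intervention mean change of 4 points in the AUDIT score". The calculation behind this is a two-sided 5% comparison of two unrelated arms with an SD of 6. It takes its inputs from an earlier Australian survey that supplied AUDIT score estimates. It allows for 20% attrition, so 50 randomised and 40 complete per arm. No correlation between time points is given.

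Two further facts bear on the AUDIT. Entry requires participants to "Score eight or above on the AUDIT" (Eligibility criteria). Items three to ten refer to the past year at T1, but to four weeks at T2 and 12 weeks at T3 (Alcohol use and severity).

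**The concern.** Randomisation guarantees that the two arms have the same expected T1 value. A model that still estimates a separate T1 mean for each arm discards that knowledge. Its group-by-time contrast then subtracts the whole observed T1 difference, although only the fraction given by the regression of follow-up on T1 is expected to carry forward.

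Two things follow, and they are one issue seen from two sides. The standard error is larger than it need be. And, given the T1 difference that actually arises, the estimate is pulled in the opposite direction. In a trial of 50 per arm that expects difficulty in recruiting (Discussion), precision available from data already collected is worth having. The choice affects each numerical outcome that has a T1 value.

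**Working it through.** **Plan's own figure.** Two-sample comparison, n = 40 per arm, difference 4, SD 6: SE = 6 × √(2/40) = 1.34. Power is 83.8% (noncentral t, 78 df) or 84.6% (normal approximation). The stated 84% reproduces.

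**What the stated model estimates.** Two arms by three times gives six cell means, and group, time and their interaction fit all six freely. With complete data the fitted means are the observed means whatever within-person covariance is used. The T2 interaction is therefore the raw difference in mean change from T1.

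**Inputs.** SD 6, 4 points, and 50 at T1 with 40 followed per arm (Power analysis). Assumed: equal SD at T1 and follow-up, and T1-T2 correlation ρ of 0.3, 0.5 or 0.7, with compound symmetry.

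**Variances at T2**, with 40 complete and 10 T1-only participants per arm:

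- Stated model, interaction: 2 × 36 × [(1 − ρ²)/40 + (1 − ρ)²/50]
- Common T1 mean: 2 × 36 × (1 − ρ²)/40

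At ρ = 0.3 these are 72 × (0.02275 + 0.0098) = 2.34 and 72 × 0.02275 = 1.64, a ratio of 1.43. Power = Φ(4/SE − 1.96).

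| ρ | SE, stated model | SE, common T1 mean | Variance ratio | Power, stated model | Power, common T1 mean |
|---|---|---|---|---|---|
| 0.3 | 1.53 | 1.28 | 1.43 | 74% | 88% |
| 0.5 | 1.31 | 1.16 | 1.27 | 86% | 93% |
| 0.7 | 1.02 | 0.96 | 1.14 | 97% | 99% |

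In the 40 completers alone the variance ratio is 2/(1 + ρ): 1.54, 1.33 and 1.18.

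**Effect of a chance imbalance.** Each point by which the intervention arm exceeds control at T1 moves the interaction estimate by −(1 − ρ). The SE of the T1 difference is 6 × √(2/50) = 1.2 points. A one-SE imbalance thus moves the estimate by 0.84 points at ρ = 0.3 (21% of the 4-point target) and by 0.60 at ρ = 0.5 (15%).

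**If the entry cut shrinks the T1 SD.** Let b be the slope of T2 on T1, with residual variance 36(1 − b²) unaffected by selection, and assume a T1 SD of 4. In completers:

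- Change variance: (1 − b)² × 16 + 36(1 − b²)
- b = 0.3: 7.84 + 32.76 = 40.6. Ratio to the adjusted variance: 40.6/32.76 = 1.24. Change-score power 79%, against 70% with a T1 SD of 6.
- b = 0.5: 4 + 27 = 31. Ratio: 31/27 = 1.15. Power 89%, against 84%.
- One-SE imbalance shift (T1 SE = 4 × √(2/50) = 0.8): 0.56 and 0.40 points.

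**The case against.** The model is standard and valid. Several stronger readings are tempting, and the document does not support them.

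- *Baseline is ignored.* It is not. The interaction subtracts T1 in full, and when ρ exceeds 0.5 that is more precise than comparing follow-up scores alone. The fault is inefficient adjustment.
- *Imbalance biases the trial.* Only conditionally on the T1 difference observed. Over randomisations the estimate is unbiased and its standard error already includes this variation.
- *The AUDIT entry cut lowers power by lowering the correlation.* Selection also narrows the T1 SD. In the calculation with a T1 SD of 4, change-score power rises and the loss against adjustment shrinks. The differing recall windows are a better reason to expect a modest correlation, but they do not supply a value.
- *The 84% belongs to another comparison.* Not shown. A source that gives score estimates suggests a single-score SD, but the target is worded as a "post-intervention mean change of 4 points in the AUDIT score". If SD 6 is the SD of a change, 84% fits the T2 change contrast in 40 completers per arm. If it is a score SD, power may be below or above 84%, depending on ρ.
- *The baseline tests decide whether to adjust.* The article describes those tests but does not give them that role.

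It is also fair that the article never names the interaction as the effect. Reading the T2 group difference from the same model instead gives power of 85%, 86% and 88% at ρ = 0.3, 0.5 and 0.7, still below 88%, 93% and 99%. What stands against the objections is that the model is stated, not left open, and a more precise one is available at no cost.

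**Conclusion.** The point holds as one of efficiency and clarity, not validity. The stated model gives a pre-randomisation measure free arm means, and its natural contrast is a change-score difference. With equal SDs of 6, its variance exceeds that of a common-baseline model by 43%, 27% and 14% at assumed correlations of 0.3, 0.5 and 0.7. The corresponding loss of power for 4 AUDIT points is about 14, 7 and 2 percentage points. The direction does not depend on the correlation so long as it is below 1. The size does, and it also depends on the T1 SD: with an assumed T1 SD of 4 the completers-only excess is 24% at slope 0.3 and 15% at slope 0.5. The trial is not shown to be underpowered. The power statement is ambiguous because it does not say what SD 6 measures.

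**What to change.** **Data analysis.** For each numerical outcome with a comparable T1 value, do one of the following:

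- keep T1 as a response but drop the group main effect, so that both arms share one T1 mean and group differences enter only at T2 and T3, with an unstructured within-person covariance; or
- model T2 and T3 only, with T1 as a covariate crossed with time.

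The unstructured covariance matters in the first option, because with a random intercept alone the adjustment slope is dictated by the covariance model. The covariate option estimates its own slope at each time. Name the T2 and T3 group contrasts as the effects, and apply the model whatever the baseline tests show. Frequency of service use has no comparable T1 value, since T1 asks only which services are in current use, so it falls outside this change.

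**Power analysis.** State whether SD 6 is the SD of a score or of a change, and restate the AUDIT power for the chosen contrast over a range of assumed T1-T2 correlations.

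**Cost.** One line of model wording and one revised power sentence, with no new data or participants. Data collection is described as ongoing, so the change should be dated before outcomes are compared by arm.

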### Power analysis

The target sample size is 50 participants per group. Assuming 20% attrition rate, we estimate to collect complete data from 40 participants in each group. Sample size calculations are based on the only available Australian study of alcohol consumption in this population, the Australian Alcohol and lesbian/bisexual women – insights into culture and emotions (ALICE) study [1], which provides estimates for the AUDIT score. A sample size of 40 participants per group has 84% power for detecting a post-intervention mean change of 4 points in the AUDIT score, when the standard deviation is assumed as 6 for two independent groups, two-tailed test, and significance level 0.05. This sample size will achieve 80% power to detect effect sizes larger than 0.63 for any of the other scores outcomes.

## Discussion

SSAW tend to drink more than heterosexual women but are generally less likely to seek treatment [4, 24, 60, 61]. There are a range of barriers to SSAW accessing treatment [1], including a reluctance to attend mainstream clinical services, reports of low satisfaction with their care in these services, and difficulty finding services that are culturally tailored, sensitive and meet their needs [5–8]. Thus, an alcohol intervention that is culturally tailored and aware of issues specific to SSAW has the potential to increase access to support.

Few alcohol support services exist in Australia which are culturally tailored to SSAW or LGBT individuals. *Thorne Harbour Health* [62] run a therapeutic group for SSAW called *Drink Limits* and LGBT specific Alcoholics Anonymous (AA) meetings are available. However, limitations exist for many SSAW as these services are mainly urban based, and anonymity is reduced as the LGBT population is quite small. Thus, it is not surprising that in an Australian study exploring SSAW’s help-seeking preferences and behaviour (*n* = 1706), 55% of respondents reported that they use the internet for informal support [63]. SMS appears to be a viable option given research highlighting SMS as an effective method for delivering brief alcohol interventions in mainstream samples [13], as well as it overcoming many help-seeking barriers, including the option for anonymity, and broad access for women in both urban and rural locations.

The Step One Program was therefore developed using an Intervention Mapping framework to guide the process. While the co-design of this intervention is believed to increase the likelihood that SSAW will engage with it [64], we anticipate facing a number of operational issues during this study. Foremost is the potential difficulty recruiting the targeted number of participants given that minority groups can be difficult to reach [65, 66]. This is addressed by advertising the study in a variety of LGBT-specific and mainstream locations as described above under ‘Participant Recruitment’. Additionally, it is anticipated that recruiting participants for an alcohol intervention may also have its challenges as research has found SSAW avoid seeking alcohol reduction support as they fear stigma and judgement relating to their sexual orientation and problem with alcohol use [1, 6]. Therefore, the majority of advertising will be online via community and social networks through email, websites, and social media as they are discrete and do not require the individual to publicly take a flyer or write down the website. Furthermore, online advertisements present fewer barriers as the individual can open the survey straight away, whereas posters and flyers rely on an individual’s motivation to type the survey link into their phone or computer at a later time.

A final potential operational issue relates to the blinding of participants. That is, the study is being conducted in accordance with the CONSORT guidelines [67] and participants are blinded to the condition they are allocated to. Nonetheless, given that participants are aware that the study is trialling the effectiveness of a set of culturally tailored SMS messages, they are likely aware of which group they have been allocated to (i.e. the intervention or control group). This may bias the results on primary outcomes due to differential reporting in the intervention group. In addition, being in the control group, which involved completing the baseline survey and receiving a weekly SMS, may be an intervention in itself and act as a placebo effect. A similar outcome was reported from a trial of an online alcohol intervention developed in the United Kingdom for the general population [68]. The researchers were unable to demonstrate a significant difference between the control and intervention groups due to the fact that everyone reduced their alcohol intake [69].

Despite these potential operational issues, the significance of this research is underlined by insufficient knowledge among health practitioners regarding the specific needs and issues unique to SSAW despite their high risk for hazardous drinking and low satisfaction with care. Therefore, the results of this study may have important implications for clinical practice and provide direction for future research. This study will be the first to develop an empirically-based alcohol intervention specifically for SSAW and to provide evidence of their response to a brief alcohol intervention. Given the unique nature of this study, it is anticipated that the findings may inform policy makers of the feasibility and acceptability of a culturally tailored alcohol intervention for SSAW. Outcomes may also highlight the role of SMS interventions to facilitate alcohol reduction for SSAW, and promote resilience and wellbeing. Finally, this study may also inform and encourage the development of other health programs that are culturally tailored to SSAW, other specific groups within the LGBT community, or other marginalised hard to reach population groups.

